## 9.6 Reporting Procedures for All Adverse Events

All local and systemic AEs occurring in the 28 days following each study vaccination observed by the Investigator or reported by the volunteer, whether or not attributed to study medication, will be recorded in electronic diaries or study database. AEs occurring following vaccination at Extra Visit B will not be recorded, unless meeting criteria for AESI or SAE. Only SAEs and AESI will be recorded for participants who are unblinded and receive an approved/licensed COVID-19 vaccine either as part of the national roll-out strategy OR vaccines administered as part of provision of treatment to controls (introduced in protocol V19.0). Participants in a subset of groups 4, 6, 9 and 10 will be asked to record local and systemic AE's for 7 days following vaccination in the electronic diary. Any unsolicited non serious AEs reported by participants in any group at subsequent routine visits will be documented on the eCRF until at least 6 months of safety data has accrued for ChAdOx1 nCoV19 (1st November 2020). All AEs that result in a volunteer's withdrawal from the study will be followed up until a satisfactory

resolution occurs (if the volunteer consents to this), or until a non-study related causality is assigned. SAEs and Adverse Events of Special Interest will be collected throughout the entire trial period.

## 9.7 Assessment of severity

The severity of clinical and laboratory adverse events will be assessed according to scales based on FDA toxicity grading scales for healthy and adolescent volunteers enrolled in preventive vaccine clinical trials, listed in the study specific working instructions and tables 14-16 below.

| Adverse Event                         | Grade | Intensity                                       |
|---------------------------------------|-------|-------------------------------------------------|
| Pain at injection site                | 1     | Pain that is easily tolerated                   |
|                                       | 2     | Pain that interferes with daily activity        |
|                                       | 3     | Pain that prevents daily activity               |
|                                       | 4     | A&E visit or hospitalization                    |
| Tenderness                            | 1     | Mild discomfort to touch                        |
|                                       | 2     | Discomfort with movement                        |
|                                       | 3     | Significant discomfort at rest                  |
|                                       | 4     | A&E visit or hospitalization                    |
| Erythema at injection site*           | 1     | 2.5 - 5 cm                                      |
|                                       | 2     | 5.1 - 10 cm                                     |
|                                       | 3     | >10 cm                                          |
|                                       | 4     | Necrosis or exfoliative dermatitis              |
| Induration/Swelling at injection site | 1     | 2.5 – 5 cm and does not interfere with activity |
|                                       | 2     | 5.1 - 10 cm or interferes with activity         |
|                                       | 3     | >10 cm or prevents daily activity               |
|                                       | 4     | Necrosis                                        |

Table 16. **Severity grading criteria for local adverse events** \*erythema  $\leq 2.5$ cm is an expected consequence of skin puncture and will therefore not be considered an adverse event

| Vital Signs                             | Grade 1
(mild) | Grade 2
(moderate) | Grade 3
(severe) | Grade 4
Potentially
Life
threatening                    |
|-----------------------------------------|-------------------|-----------------------|---------------------|------------------------------------------------------------------|
| Fever (oral)                            | 38.0°C - 38.4°C   | 38.5°C – 38.9°C       | 39.0°C - 40°C       | > 40°C                                                           |
| Tachycardia (bpm)*                      | 101 - 115         | 116 – 130             | >130                | A&E visit or
hospitalisation
for arrhythmia                |
| Bradycardia (bpm)**                     | 50 – 54           | 45 – 49               | <45                 | A&E visit or
hospitalisation
for arrhythmia                |
| Systolic hypertension (mmHg)            | 141 - 150         | 151 – 155             | ≥155                | A&E visit or
hospitalization
for malignant
hypertension |
| Diastolic hypertension (mmHg)           | 91 - 95           | 96 – 100              | >100                | A&E visit or
hospitalization
for malignant
hypertension |
| Systolic hypotension
(mmHg)***       | 85 - 89           | 80 – 84               | <80                 | A&E visit or
hospitalization
for
hypotensive
shock   |
| Respiratory Rate –breaths per
minute | 17 - 20           | 21-25                 | >25                 | Intubation                                                       |

Table 17. **Severity grading criteria for physical observations (applies to adults only).** \*Taken after ≥10 minutes at rest \*\*When resting heart rate is between 60 – 100 beats per minute. Use clinical judgement when characterising bradycardia among some healthy subject populations, for example, conditioned athletes. \*\*\*Only if symptomatic (e.g. dizzy/ light-headed)

|                |                                                                                                                                        |
|----------------|----------------------------------------------------------------------------------------------------------------------------------------|
| GRADE 0 | None                                                                                                                                   |
| GRADE 1 | Mild: Transient or mild discomfort (< 48 hours); No interference with activity; No medical intervention/therapy required               |
| GRADE 2 | Moderate: Mild to moderate limitation in activity – some assistance may be needed; no or minimal medical intervention/therapy required |
| GRADE 3 | Severe: Marked limitation in activity, some assistance usually required; medical intervention/therapy required.                        |
| GRADE 4 | Potentially Life-threatening: requires assessment in A&E or hospitalisation                                                            |

Table 18. *Severity grading criteria for local and systemic AEs*. NB: A&E assessment in itself does not constitute a SAE. Refer to 9.1.3 for SAE definition

## 9.8 Reporting Procedures for Serious AEs

In order to comply with current regulations on SAE reporting to regulatory authorities, the event will be documented accurately and notification deadlines respected. SAEs will be reported on the SAE forms to members of the study team immediately the Investigators become aware of their occurrence, as described in SOP OVC005 Safety Reporting for CTIMPs. Copies of all reports will be forwarded for review to the Chief Investigator (as the Sponsor's representative) within 24 hours of the Investigator being aware of the suspected SAE. The DSMB will be notified of SAEs that are deemed possibly, probably or definitely related to study interventions; the chair of DSMB will be notified immediately (within 24 hours) of the sponsor being aware of their occurrence. SAEs will not normally be reported immediately to the ethical committee(s) unless there is a clinically important increase in occurrence rate, an unexpected outcome, or a new event that is likely to affect safety of trial volunteers, at the discretion of the Chief Investigator and/or DSMB. In addition to the expedited reporting above, the Investigator shall include all SAEs in the annual Development Safety Update Report (DSUR) report.

**Grade 4 laboratory AEs** should be reported as SAEs and under the category of outcome of an important medical event. A&E attendances should not routinely be reported as SAEs unless they meet the SAE definition described above.

**Cases falling under the Hy's Law should be reported as SAEs.** A Hy's Law Case is defined by FDA Guidance for Industry "Drug-Induced Liver Injury: Premarketing Clinical Evaluation" (2009). Any study participant with an increase in Aspartate Aminotransferase (AST) or **Alanine Aminotransferase (ALT)  $\geq 3\times$  Upper Limit of Normal (ULN) together with Total Bilirubin  $\geq 2\times$ ULN, where no other reason can be found to explain the combination of these abnormal results**, e.g., elevated serum alkaline phosphatase (ALP) indicating cholestasis, viral hepatitis A, B or C, another drug capable of causing the observed injury, amongst others.

## 9.9 Reporting Procedures for SUSARS

All SUSARs will be reported by the sponsor delegate to the relevant Competent Authority and to the REC and other parties as applicable. For fatal and life-threatening SUSARS, this will be done no later than 7 calendar days after the Sponsor or delegate is first aware of the reaction. Any additional relevant information will be reported within 8 calendar days of the initial report. All other SUSARs will be reported within 15 calendar days.

Principal Investigators will be informed of all SUSARs for the relevant IMP for all studies with the same Sponsor, whether or not the event occurred in the current trial.

## 9.10 Development Safety Update Report

A Development Safety Update Report (DSUR) will be prepared annually, within 60 days of the anniversary of the first approval date from the regulatory authority for each IMP. The DSUR will be submitted by the CI to the Competent Authority, Ethics Committee, HRA (where required), Host NHS Trust and Sponsor.

## 9.11 Procedures to be followed in the event of abnormal findings

Eligibility for enrolment in the trial in terms of laboratory findings will be assessed by clinically qualified staff. Abnormal clinical findings from medical history, examination or blood tests will be assessed as to their clinical significance throughout the trial. Laboratory AEs will be assessed using specific toxicity grading scales adapted from the FDA Toxicity Grading Scale for Healthy Adult and Adolescent Volunteers Enrolled in Preventive Vaccine Clinical Trials. Paediatric laboratory AEs will be assessed using site specific paediatric laboratory reference ranges, values outside of these age

specific ranges will be reviewed by a study clinician to determine clinical significance. If a test is deemed clinically significant, it may be repeated, to ensure it is not a single occurrence. If a test remains clinically significant, the volunteer will be informed and appropriate medical care arranged as appropriate and with the permission of the volunteer. Decisions to exclude the volunteer from enrolling in the trial or to withdraw a volunteer from the trial will be at the discretion of the Investigator

### **9.12 Interim Safety Reviews**

The safety profile will be assessed on an on-going basis by the Investigators. The CI and relevant Investigators (as per the trial delegation log) will also review safety issues and SAEs as they arise.

Immunopathology data from pre-clinical and phase 1 studies will be assessed by the CI, relevant investigators and the DSMB as soon as they are available and before any volunteers receive a dose of the IMP.

The DSMB will evaluate frequency of events, safety and efficacy data every 4-8 weeks and/or as required. The DSMB will make recommendations concerning the conduct, continuation or modification of the study.

In particular, the DSMB will review the data at the following key timepoints:

- Before vaccination of the first participant (all accumulated data available will be reviewed from COV001, with a minimum 4 weeks safety and immunogenicity data from the first 54 participants receiving the IMP and all accumulated data from the animal studies)
- Prior to expansion of the recruitment of groups 4 and 6 in those aged older than 55 years (data will be reviewed from groups 1 and 2)

### **9.13 Data Safety Monitoring Board**

The Data Safety Monitoring Board that is in place for COV001 will also oversee COV002 and review data from both studies combined

The chair of the DSMB may be contacted for advice and independent review by the Investigator or trial Sponsor in the following situations:

- Following any SAE deemed to be possibly, probably or definitively related to a study intervention.
- Any other situation where the Investigator or trial Sponsor feels independent advice or review is important.

The DSMB will review SAEs deemed possibly, probably or definitively related to study interventions. The DSMB will be notified within 24 hours of the Investigators' being aware of their occurrence. The DSMB can recommend placing the study on hold if deemed necessary following a study intervention-related SAE.

The DSMB will only be able to judge the short-term safety of the ChAdOx1 nCoV-19 vaccine. Given the complexity of the underlying immunology and the minimal immunological data that will be available for review early in the study, the DSMB will not be in a position to comment on the effects of a later wave of SARS-CoV-2 as vaccine-induced immunity wanes and the theoretical risk of immune enhancement increases.

#### **9.14 Safety Group Holding Rules**

These safety holding rules apply to ChAdOx1 nCoV-19 vaccine only. Solicited, unsolicited and laboratories adverse events will be systematically collected in groups 1, 2, 5, 7 and 8. A sub-set of up to 1000 participants in each of Groups 4, 6, 9 and 10 will be asked to record solicited and unsolicited AEs for 7 days only.

- **Solicited local adverse events:**
  - If more than 25% of doses of the vaccine at a given time point (e.g. Day 0, Day 28) in a study group are followed by the same Grade 3 solicited local adverse event beginning within 2 days after vaccination (day of vaccination and one subsequent day) and persisting at Grade 3 for >72 hrs
- **Solicited systemic adverse events:**
  - If more than 25% of doses of the vaccine at a given time point (e.g. Day 0, Day 28) in a study group are followed by the same Grade 3 solicited systemic adverse event beginning within 2 days after vaccination (day of vaccination and one subsequent day) and persisting at Grade 3 for >72 hrs

- **Unsolicited adverse events:**
  - If more than 25% of doses of the vaccine at a given time point (e.g. Day 0, Day 28) in a study group are followed by the same Grade 3 unsolicited adverse event beginning within 2 days after vaccination (day of vaccination and one subsequent day) and persisting at Grade 3 for >72 hrs
- **Laboratory adverse event:**
  - If more than 25% of doses of the vaccine at a given time point (e.g. Day 0, Day 28) in a study group are followed by the same Grade 3 laboratory adverse event beginning within 3 days after vaccination and persisting at Grade 3 for >72 hrs
- **A serious adverse event considered possibly, probably or definitely related to vaccination occurs**
  - If an SAE occurs in any one individual, which is possibly, probably or definitely related to vaccination this would trigger a holding rule. There are two exemptions from this rule, which would not activate a holding rule. These include:
    - COVID-19 related hospital admissions considered to be at least possibly related to ChAdOx1 nCoV-19 (e.g. if considered to be a clinical presentation of a disease enhancement episode). COVID-19 related SAEs will be regularly reviewed by the DSMB, and a single event will not trigger a holding rule.
    - SAEs reported under the Hy's Law requirement will not necessarily trigger a holding rule. These cases will also be reviewed by the DSMB

If any of the above holding rules are activated, then further vaccinations in any of the groups will not occur until a safety review by the DSMB, study sponsor and the chief investigator has been conducted and it is deemed appropriate to restart dosing. The Regulatory Authority will be informed and a request to restart dosing with pertinent data will be submitted as a substantial amendment. The safety review will consider:

- The relationship of the AE or SAE to the vaccine.
- The relationship of the AE or SAE to the vaccine dose, or other possible causes of the event.

- If appropriate, additional screening or laboratory testing for other volunteers to identify those who may develop similar symptoms and alterations to the current Participant Information Sheet (PIS) are discussed.
- New, relevant safety information from ongoing research programs on the various components of the vaccine.

The local ethics committee and vaccine manufacturers will also be notified if a holding rule is activated or released.

All vaccinated volunteers will be followed for safety until resolution or stabilisation (if determined to be chronic sequelae) of their AEs.

Since the approval of ChAdOx1 nCoV-19 for emergency use by the MHRA and its subsequent national roll-out, group holding rules will no longer apply. Any SUSARs occurring in the trial from the time of approval onwards will be notified to and discussed with the DSMB and the MHRA, but will no longer automatically trigger a holding rule.

#### **9.14.1 Individual stopping rules (will apply to prime-boost groups only)**

In addition to the above stated group holding rules, stopping rules for individual volunteers will apply (i.e., indications to withdraw individuals from further vaccinations). Study participants who present with at least one of the following stopping rules will be withdrawn from further vaccination in the study:

- **Local reactions:** Injection site ulceration, abscess or necrosis
- **Laboratory AEs:**  
the volunteer develops a Grade 3 laboratory AE considered possibly, probably or definitely related within 7 days after vaccination and persisting continuously at Grade 3 for > 72hrs.
- **Systemic solicited adverse events:**
  - the volunteer develops a Grade 3 systemic solicited AE considered possibly, probably or definitely related within 2 days after vaccination (day of vaccination and one subsequent day) and persisting continuously at Grade 3 for > 72hrs.
- **Unsolicited adverse events:**

- the volunteer has a Grade 3 adverse event, considered possibly, probably or definitely related to vaccination, persisting continuously at Grade 3 for >72hrs.
- the volunteer has a SAE considered possibly, probably or definitely related to vaccination.
- the volunteer has an acute allergic reaction or anaphylactic shock following the administration of vaccine investigational product.

If a volunteer has an acute respiratory illness (moderate or severe illness with or without fever) or a fever (oral temperature greater than 37.8°C) at the scheduled time of administration of investigational product/control, the volunteer will not be enrolled and will be withdrawn from the study.

All vaccinated volunteers will be followed for safety until the end of their planned participation in the study or until resolution or stabilisation (if determined to be chronic sequelae) of their AEs, providing they consent to this.

Participants who met individual holding rules or were advised not to receive a booster dose as a result of an AE and have been offered a COVID-19 approved/licensed vaccine will be given an opportunity to discuss potential safety implications if they were to accept the offered vaccine with clinically qualified investigators.

In addition to these pre-defined criteria, the study can be put on hold upon advice of the DSMB, Chief Investigator, Study Sponsor, regulatory authority, Ethical Committee(s), for any single event or combination of multiple events which, in their professional opinion, jeopardise the safety of the volunteers or the reliability of the data.

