After review of all available data from animal studies and at least 4 weeks safety and immunogenicity data from the first 54 participants receiving ChAdOx1 nCoV-19 in COV001, following DSMB review, enrolment into Groups 1, 4, 5 & 6 will commence. A minimum of 7 days safety data from group 1 will be reviewed by the DSMB prior to enrolment of participants into group 2. Participants will be randomised to ChAdOx1 nCoV-19/MenACWY on a 3:1:3:1 ratio in groups 1 and 7, and 5:1:5:1 ratio in groups 2 and 8, 1:1 in groups 4, 5a, 5b, 5c, 6, 9 and 10, and 5:1 in group 5d. Groups 5e and 5f will be open label and therefore, volunteers will not be randomised. Participants in groups 4, 6, 9 and 10 will be advised to take prophylactic paracetamol for 24 hours (1000 mg every 4-6 hours) from the time of vaccination to reduce the likelihood of fever. The sequence of enrolment of participants over the age of 56 years is outlined in section 7.3.2.2. Up to 100 volunteers in group 4 will be invited to receive a booster dose of  $2.2 \times 10^{10}$  vp (qPCR) 4-6 weeks after prime. All remaining volunteers in group 4 and all participants in group 6 will be invited to receive a booster dose of 0.5mL ( $3.5 - 6.5 \times 10^{10}$  vp, Abs 260, corrected for PS80) at least 4 weeks after prime. Participants who were originally randomised to receive a single dose in groups 1 (a1 and a2), 2 (a1 and a2) and 5 (a1 and a2) will be invited to receive a booster dose of 0.5mL ( $3.5 - 6.5 \times 10^{10}$  vp, Abs 260, corrected for PS80) at the earliest available opportunity, with a minimum 4 weeks interval from prime.

Safety will be assessed in real time. The DSMB will periodically assess safety and efficacy data every 4-8 weeks and/or as required.

Participants will be followed over the duration of the study to record adverse events and episodes of virologically confirmed symptomatic COVID-19 cases. Participants will be tested for COVID-19 if they present with a new onset of fever ( $\geq 37.8$  C) OR cough OR shortness of breath OR anosmia/ageusia.

Weekly testing for PCR+ infection with SARS-CoV-2 using home test kits will also be undertaken in partnership with the Department of Health and Social care national community testing programme, subject to testing resource availability.

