Moderate and Severe COVID-19 disease will be defined using clinical criteria. Detailed clinical parameters will be collected from medical records and aligned with agreed definitions as they emerge. These are likely to include, but are not limited to, oxygen saturation, need for oxygen therapy, respiratory rate and other vital signs, need for ventilatory support, Xray and CT scan imaging and blood test results, amongst other clinically relevant parameters.

Accumulated safety data from COV001 will be reviewed before commencing enrolment.

To account for the multisite recruitment activity, it is recognised that the number of volunteers enrolled into each group 9 and 10 will be 1000 +/-10%.

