## **5.2 Trial volunteers**

Adult volunteers aged at least 18 years, will be recruited into the study. Volunteers will be considered enrolled immediately following administration of the vaccine.

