### 6.3.3 Re-vaccination exclusion criteria

The following AEs associated with any vaccine, or identified on or before the day of vaccination constitute absolute contraindications to further administration of an IMP to the volunteer in question. If any of these events occur during the study, the subject will not be eligible to receive a booster dose and will be followed up by the clinical team or their GP until resolution or stabilisation of the event:

- Anaphylactic reaction following administration of vaccine
- Pregnancy. An exception to this will be prior to receipt of a booster dose at extra visit B. If a pregnant woman has discussed vaccination with their usual clinician (e.g. GP) and chooses to receive a COVID-19 vaccination, this may be administered by the trial team as part of extra visit B (*Protocol 19.0:*) or as part of the provision of treatment to controls.
- Any AE that in the opinion of the Investigator may affect the safety of the participant or the interpretation of the study results

Participants who develop COVID-19 symptoms and have a positive NAAT test after the first vaccination can only receive a booster dose after a minimum 4 weeks interval from their first NAAT positive test, provided their symptoms have significantly improved. The decision to proceed with booster vaccinations in those cases will be at clinical discretion of the investigators. For participants who are asymptomatic and have a positive NAAT test, a minimum of 2 weeks from first NAAT positivity will be required before boosting.

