### **7.3.2 Day 0: Enrolment and vaccination visit**

Participants in all groups will have informed consent taken as per section 6.2. Volunteers will be considered enrolled in to the trial at the point of vaccination. Before vaccination/trial intervention, the eligibility of the volunteer will be reviewed. Temperature will be observed and if necessary, a medical history and physical examination maybe undertaken to determine need to postpone vaccination or withdraw the participant. Vaccinations/trial intervention will be administered as described below.

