#### **7.3.4.2 COVID-19 testing visit**

Participants will be invited for a COVID-19 testing visit in two circumstances:

- They report primary endpoint symptoms AND have not already had a documented negative SARS-CoV-2 NAAT test result (including trial weekly swabs and tests performed outside of the trial) since their symptom onset
- They report primary endpoint symptoms and have had a positive SARS-CoV-2 NAAT test from their trial weekly swab test or from outside of the trial since symptom onset

At the COVID-19 testing visit, a nose/throat and immunology bloods (paxgenes, cytokine profile, PBMCs, serum and others, according to local site capacity) will be acquired. Clinical assessments may be performed at COVID-19 testing visits at the discretion of investigators. Symptomatic volunteers may be regularly reviewed over the phone or via video call using a smartphone or computer app if clinically appropriate. Participants who have a positive NAAT will be reviewed by phone for symptom severity data at approximately 7 days post positive swab. Closer follow-up and safety monitoring may be carried out by local trial teams if felt this is clinically indicated. Symptomatic participants with a positive NAAT test outside of the trial or as part of their trial weekly swab tests will be asked to attend for a COVID-19 testing visit in order to take a further swab to facilitate SARS-CoV-2 sequencing and additionally to acquire immunology bloods.

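### The closing rule of section 9.14.1 is worded for Day 0, but read literally it also withdraws from the study an enrolled participant who is ill at the boost visit

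*Protocol*

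**What the plan says.** Protocol section 9.14.1 is headed as applying to prime-boost groups only. It introduces its rules as reasons to stop vaccinating an individual: a participant who meets one "will be withdrawn from further vaccination in the study". The bulleted rules cover local reactions, laboratory and solicited events, related serious adverse events and acute allergic reactions.

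A separate paragraph follows the bullets. It covers moderate or severe acute respiratory illness, with or without fever, and oral temperature above 37.8°C, when product or control is due to be given. In that case "the volunteer will not be enrolled and will be withdrawn from the study". The next paragraph keeps vaccinated volunteers under safety follow-up.

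Other sections bear on the same situation:

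- Section 5.2: "Volunteers will be considered enrolled immediately following administration of the vaccine".
- Section 7.3.2, before the Day 0 dose: temperature is taken and, if needed, history and examination are used "to determine need to postpone vaccination or withdraw the participant".
- Section 6.3.3, repeated in 7.3.4.4: a participant with COVID-19 symptoms and a positive test after the first dose "can only receive a booster dose after a minimum 4 weeks interval from their first NAAT positive test", once symptoms have improved and at the investigators' discretion.
- Section 6.3.3 also bars the booster for any adverse event that the investigator thinks may affect safety or interpretation. Clinical follow-up then runs until the event resolves or stabilises.
- Section 6.3.5.1: a participant for whom the study load is too heavy may drop procedures, the booster dose among them, and remain in the study.

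**The concern.** The sentence mixes two situations. Its consequence is partly one that only a person not yet vaccinated can suffer, but its trigger is any scheduled dose and its heading names the groups that have two. A site that applies it literally at a boost visit would remove a randomised, already vaccinated participant from the study because of a temporary illness.

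Fever at a boost visit is also exactly what the efficacy follow-up is meant to catch. Section 5 says "Participants will be tested for COVID-19 if they present with a new onset of fever" of at least 37.8°C, so any new fever that triggers the 9.14.1 rule also triggers a COVID-19 test. Withdrawal at that moment would stop efficacy follow-up just when a possible endpoint case is being investigated. It would also remove the chance of a deferred second dose and, with it, a place in the two-dose primary analysis.

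**Working it through.** No arithmetic applies. The check is whether the sentence can be read consistently with the rest of the protocol, first at Day 0 and then at the boost visit.

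**1. Which visits does the sentence reach?** Under 5.2 and 7.3.2 a volunteer becomes enrolled at vaccination on Day 0. The non-enrolment half of the consequence can therefore operate only before the first dose. The trigger is the planned time of giving product or control, and in prime-boost groups that occurs twice. No words restrict it to the first. A rule meant only for Day 0 would also have no reason to sit in a section confined to prime-boost groups, since single-dose volunteers need it equally. The sentence is therefore probably a misplaced Day 0 rule, but its location and trigger leave the boost visit inside its literal scope.

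**2. Day 0.** Section 7.3.2 gives two outcomes, postponement or withdrawal. Section 9.14.1 gives withdrawal only. This is an omission more than a contradiction: withdrawal is one of the two outcomes in 7.3.2, and no enrolled participant is lost.

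**3. Boost visit, symptomatic and NAAT positive.** Sections 6.3.3 and 7.3.4.4 say wait at least 4 weeks, then decide clinically. Section 9.14.1 says leave the study. Both cannot be followed, and the text does not say which prevails.

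**4. Boost visit, ill but not NAAT positive.** Section 6.3.3 has no specific deferral interval for this case. Its investigator-discretion clause allows the booster to be withheld with clinical follow-up, without study withdrawal. The 9.14.1 sentence conflicts with that outcome and with the section's own purpose of stopping vaccination only.

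**5. Boost visit, asymptomatic and NAAT positive.** The 2-week interval in 6.3.3 is not in conflict, because a person without illness or fever does not meet the 9.14.1 trigger.

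**6. Is study withdrawal needed for a missed boost?** No. Section 6.3.5.1 is written for participants burdened by visits, not for illness, but it shows that the protocol regards a missed boost as compatible with continued safety, immunogenicity and efficacy data.

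**7. What would a literal withdrawal lose?** Section 6.3.5 keeps data and samples collected beforehand in the analysis and continues long-term safety collection. It does not provide for continued efficacy follow-up. The participant would have no second dose and so no place in the two-dose primary analysis (Statistics, Primary efficacy). In the secondary analysis of at least one standard dose, cases count from more than 21 days after a standard-dose prime. A boost due at least 4 weeks after prime falls inside that period, so time at risk up to withdrawal is kept and later time is lost.

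**The case against.** The strongest reply is that the sentence limits itself. Its two consequences are joined, and a person already enrolled cannot fail to be enrolled, so the boost reading discards half of it. The heading names groups, not visits, and those groups also have a Day 0. The sentence stands outside the bulleted stopping rules. Boost visits have their own provisions in 6.3.3, 7.3.4.2 and 7.3.4.4, and a sensible site would follow those. This is largely right about intent, and it is why the sentence is best seen as a misplaced Day 0 rule. It does not remove the defect: the trigger and the section still cover the boost visit, and no text gives the specific boost provisions precedence.

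A reader might also infer that the rule has cost the trial participants or biased vaccine efficacy. The documents do not support that. They show no one withdrawn under it, give no rate of illness at boost visits, and offer no reason to expect a difference between arms. The number of people due a boost would not measure the effect either, since it counts who could be exposed to the sentence and not who was withdrawn.

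A reader might further infer that all data on a withdrawn participant are lost, or that transient fever is treated more harshly than anaphylaxis throughout. The first is wrong, because 6.3.5 retains earlier data and safety collection continues. The second holds only on the literal boost-visit reading.

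Finally, little remains to be protected. Section 7.6.1 records that the primary efficacy analysis is complete and that all participants are unblinded from V19.0. Doses given to controls after that are screened against national guidance (the schedule for unblinding and treatment of controls, after section 7.3.3). This stands and limits the point to a minor one.

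**Conclusion.** The closing rule of 9.14.1 is wrong as written. It states a Day 0 consequence under a heading and trigger that also cover the boost visit. Followed literally there, it needlessly ends participation for a transient illness, against the section's own purpose and against 6.3.3, 7.3.4.4 and 6.3.5.1. At Day 0 it leaves out postponement.

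The size is minor, and the number affected is unknown. An amendment cannot alter the completed primary efficacy analysis. What could still be touched is any withdrawal already made under the sentence, as it bears on the supportive final analysis, and any second dose still to be given, for example at Extra Visit B (7.6.2). The conclusion rests on a literal reading. If every site treated the sentence as a Day 0 rule and followed 6.3.3 at boost visits, no participant was affected. The withdrawal reasons that 6.3.5 requires in the CRF would show whether that was so.

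**What to change.** Limit the sentence to the Day 0 visit before enrolment and bring it into line with 7.3.2: for moderate or severe acute respiratory illness or fever, postpone the dose or do not enrol. It would sit better in 7.3.2, where it would apply to all groups.

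For boost visits, state separately: defer or omit the dose; test under 7.3.4, where the first condition for a testing visit is "They report primary endpoint symptoms AND have not already had a documented negative SARS-CoV-2 NAAT test result"; apply the interval in 6.3.3 and 7.3.4.4 if the test is positive; and keep the participant in study follow-up whether or not the dose is later given.

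The cost is one reworded rule in the next amendment. It adds no visits, samples or procedures, because testing, deferral and continued follow-up already exist in the protocol.
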